### **13.5 Subjects who Become Pregnant**

In the unlikely event that a subject becomes pregnant during the study, she will discontinue study product use immediately. Procedures to be followed to ensure the subject's safety (and that of the fetus), including pelvic sampling, will be determined based on the investigator's judgment.

### 13.6 Protocol Deviations and Violations

All protocol violations and deviations will be recorded in source documentation and the Population Council will be immediately notified of all violations and deviations upon the site's awareness. Protocol deviations and violations will be reviewed by the Council Medical Monitor who will decide on a resolution.

## 14. SAFETY ASSESSMENTS

### 14.1 Safety Monitoring

AEs and SAEs will be carefully monitored and recorded throughout this study. The Investigator is responsible for continuous close safety monitoring of all subjects, and for alerting the Population Council (referred to hereafter as Sponsor) if any concerns arise. Subjects will be instructed to contact the study site staff to report any AEs they may experience. At every visit, study staff will ask each subject how they felt since their last visit, and ask if they have experienced any AEs.

The term "investigational product" for this study refers to PC-6500 or PC-535 placebo.

Subjects will also be asked if they have used any new medications, or changed any current medication regimens (both prescription and OTC medications).

### 14.2 Adverse Events Definitions and Reporting Requirements

#### 14.2.1 Definition of Terms

**Adverse Event:** An AE is defined as any untoward medical occurrence associated with the use of a drug in humans, whether or not considered drug related. As such, an AE can be an unfavorable or unintended sign (including an abnormal laboratory finding), symptom or disease temporally associated with the use of investigational product or study participation, whether or not considered related to the product or study participation. In addition to novel events, an AE may be an exacerbation of a pre-existing medical condition that was present prior to study entry. This definition will be applied from the time a potential subject signs the ICF.

**Treatment Emergent Adverse Events (TEAEs)** are defined as any AE that begins on or after the first dose of the study drug and up to seven days after the final study drug dose, or pre-existing conditions that worsened during the same timeframe.

**Non-Treatment Emergent AEs** are defined as those reported between the date the informed consent form was signed and the first dose of study drug, and more than seven days after the last study drug dose.

#### 14.2.2 Exacerbation of Pre-Existing Medical Condition

An increase in the frequency or severity/intensity of a medical condition that is present before study consent should be reported as an AE. Any medical condition that is present before study consent and that does not deteriorate should not be reported as an AE.

#### 14.2.3 Reporting Period for Adverse Events

The reporting period for AEs is the period immediately following the signing of the ICF through seven days after the final dose in the OL period and through 14 days after the final dose in the randomized period of the study.

For the purpose of data analysis, if a non-serious AE has not resolved at the end of the study-reporting period, it will be documented as still ongoing in the CRFs. However, the Investigator must make every effort to follow the event to stabilization or resolution and report the findings/outcome to the Sponsor as soon as possible. A minimum of 3 attempts to follow up with the subject with different methods of communication (e.g., telephone, certified mail, email) should be documented.

#### 14.2.4 Recording Adverse Events

The Investigator is responsible for assessing all AEs that occur at any time during the study. The Investigator must make a determination of relatedness, seriousness, and intensity in the CRFs for each AE.

All AEs will be recorded in the appropriate CRFs. AEs will be recorded using a recognized medical term or diagnosis that accurately reflects the event and includes the following information (when applicable):

- Date condition or event started.
- Date of resolution. If the event has not resolved at the end of the study reporting period, it will be documented as still present or ongoing in the CRFs. However, every effort should be made to obtain the outcome.
- Indication of whether the condition was pre-existing prior to study entry or not, and if yes, whether it has worsened in the severity/intensity or frequency, in which case it is reported as an AE. Conditions present prior to study entry that do not worsen in severity/intensity or frequency are not considered AEs.
- Intensity/Severity: AEs that change in intensity are recorded at the intensity level that is the most severe, as reported by the subject or observed by the Investigator.
- Relationship to investigational product, as evaluated by the Investigator.
- Possible etiologies and whether the event meets criteria as a serious adverse event (SAE) and therefore requires immediate notification to the Sponsor.
- Seriousness: If the event meets 1 or more of the regulatory criteria in the definition of an SAE (see below), the event should be classified as serious. See below for SAEs.

### 14.3 Serious Adverse Events Definitions and Reporting Requirements

#### 14.3.1 Serious Adverse Event

An AE is considered “serious” if, in the view of either the Investigator or Sponsor, it:

- Results in death.
- Is life-threatening. (This term refers to an event in which the subject was at risk of death at the time of the event; it does not refer to an event that hypothetically might have caused death if it were more severe.)
- Requires inpatient hospitalization or prolongation of existing hospitalization. (In general, hospitalization signifies that the subject has been admitted [usually involving at least an overnight stay] to the hospital or emergency ward for observation and/or treatment that would not have been appropriate in the physician’s office or outpatient setting. Complications that occur during hospitalization are AEs or SAEs as defined above. If a complication prolongs hospitalization or fulfills any other serious criteria, the event is

serious. When in doubt as to whether “hospitalization” occurred or was necessary, the AE should be considered serious. Hospitalization for elective treatment or procedures of a pre-existing condition that did not worsen from baseline is not considered an AE.)

- Results in persistent or significant disability/incapacity or substantial disruption of the ability to conduct normal life functions.
- Is a congenital anomaly/birth defect.
- Is an important medical event that may not result in death, be life threatening, or require hospitalization but, based upon appropriate medical judgment, may jeopardize the subject and may require medical or surgical intervention to prevent one of the outcomes listed in the definition above. Examples of such medical events include allergic bronchospasm requiring intensive treatment in the emergency room or at home, blood dyscrasias or convulsions that do not result in patient hospitalization, or the development of drug dependency or drug abuse.

In addition, cancer and drug overdose are included in the Sponsor’s classification of an SAE.

#### 14.3.2 Study Reporting Period for Serious Adverse Events

The reporting period for SAEs is the period immediately following the signing of the ICF through seven days after the last dose in the OL period and through 14 days after the last dose in the randomized period of the study.

SAEs must be followed until resolution, even if it extends beyond the study reporting period. Resolution of an SAE is defined as the return to baseline status or stabilization of the condition with the expectation that it will remain chronic.

#### 14.3.3 Severity/Intensity

Grading of AEs and SAEs will follow the Division of AIDS Table for Grading the Severity of Adult and Pediatric Adverse Events (DAIDS AE Grading Table), Version 2.0, November 2014. For grading female genital events, please refer to Addendum 1 (Female Genital Table for Use in Microbicide Studies), which can be found in Appendix 5.

#### 14.3.4 Relationship to Test Article

The Investigator is responsible for assessing the relationship between the AE and the investigational product. The Investigator must determine whether there is a reasonable possibility that the investigational product caused or contributed to an AE. The relationship assessment, based on clinical judgment, often relies on the following:

- A temporal relationship between the event and administration of investigational product;
- A plausible biological mechanism for the investigational product to cause the AE;
- Another possible etiology of the AE; or
- Previous report of similar AEs associated with the investigational product or other agents in the same class.

The terms used to assess the relationship of an event to the investigational product are:

| Causality Assessment | Criteria for Assessment (note: re-challenge will not be done in this study)                                                                                                                                                                                                                                                                                                                                                                              |
|-----------------------------|-----------------------------------------------------------------------------------------------------------------------------------------------------------------------------------------------------------------------------------------------------------------------------------------------------------------------------------------------------------------------------------------------------------------------------------------------------------------|
| Highly Probably Related     | The experience occurs immediately following investigational product administration, related pharmacologically (not related to underlying condition/concurrent disease or other drugs or chemicals)                                                                                                                                                                                                                                                              |
| Probably Related            | The experience follows a reasonable temporal sequence from the time of drug administration and follows a known response pattern to the suspected investigational product and cannot be reasonably explained by other factors such as the subject's clinical state, therapeutic intervention or concomitant therapy.                                                                                                                                             |
| Possibly Related            | The experience follows a reasonable temporal sequence from the time of drug administration and/or follows a known response pattern to the investigational product but could have been produced by other factors such as the subject's clinical state, therapeutic intervention or concomitant therapy.                                                                                                                                                          |
| Unlikely Related            | Improbable temporal relationship. The experience was most probably produced by other factors such as the subject's clinical state, therapeutic intervention or concomitant therapy and does not follow a known response pattern to the investigational product.                                                                                                                                                                                                 |
| Not Related                 | There is not a reasonable possibility that the AE is related to the investigational product; when an AE is assessed as not related to the investigational product, an alternative etiology, diagnosis or explanation for the AE should be provided. If new information becomes available, the relationship of any AE should be reviewed again and updated, as required.                                                                                         |
| Insufficient data to assess | Selection of this rating should usually not occur in a clinical study because the Investigators have an obligation to obtain and provide this information. In exceptional instances, this rating may be used in order to avoid delay in initial reporting of fatal or life-threatening SAEs from clinical studies. Such cases should include documentation in the comments section of the CRFs/database with rationale for why an assessment could not be made. |

#### 14.4 Notification to Sponsor of Immediately Reportable Events (IRE)

All SAEs and AEs that led to premature discontinuation from the study (Immediately Reportable Events) require immediate reporting to the Sponsor whether expected or unexpected, related or unrelated. As the Sponsor of this Investigational New Drug (IND), the Population Council is responsible for complying with the reporting requirements of SAEs to the FDA in accordance with 21 CFR 312.50. The Sponsor will be responsible for the appropriate recording, review and compliance with regulatory reporting requirements to the FDA of the SAE. When any SAE or an AE that led to premature discontinuation, regardless of causality, is encountered during this study at an Investigator's site, the Investigator must immediately notify the Sponsor by e-mail: [[contact]](mailto:[contact]).

All IRE (SAE or AE that led to premature discontinuation from the study) reports must be submitted within 24 hours from the time the site staff is notified of the event to the Population Council Safety Desk (e-mail: [[contact]](mailto:[contact]) or if there is a problem with e-mail, call: [contact]).

Additional supporting documentation for SAEs should be provided whenever possible (with subject name redacted) to verify the medical diagnosis, including hospital discharge summaries and death certificates/autopsy reports (where applicable), surgical procedure summaries, histology reports, and imaging reports.

The Investigator should cooperate and furnish additional information, including copies of pertinent records if necessary, to assist the Sponsor's personnel in their evaluation of the event.

**NOTE: Investigators should not wait to collect the additional information needed to fully document the event before submitting an IRE report to the Population Council.**

E-mail the following information to the Population Council Safety Desk (e-mail: [[contact]](mailto:[contact])):

1. IRE Report Form
2. Medical History CRFs
3. AE CRFs
4. Prior/Concomitant Medications CRFs
5. Relevant laboratory/diagnostic test results and medical record progress notes

Upon receipt of an IRE the Sponsor's Medical Safety Director will review the report promptly. SAEs will be reported to regulatory authorities in accordance with applicable national regulations and the Sponsor's SOP.

The Investigator will submit AE information in accordance with local regulatory agencies or other local authorities' requirements. This reporting will include site IRB-mandated reporting of AEs, SAEs and other relevant safety information.

## 14.5 Medical Emergencies and Emergency Protocol Deviations

In medical emergencies, the Investigator will use medical judgment and remove the subject from immediate harm. The Investigator will then immediately notify the Sponsor and the IRB regarding the type of emergency and the course of action taken.

The Investigator shall notify the Medical Safety Director, the Medical Monitor and the reviewing IRB(s) of any deviation from the investigational plan to protect the life or physical wellbeing of a subject in an emergency. Such notice shall be given as soon as possible, but in no event later than 48 hours after the emergency occurred. Except in such an emergency, prior approval by the Sponsor is required for any changes in or deviations from the protocol. All deviations must be documented.

The following contact will be used for all communications with the study Medical Safety Director:

[name]  
Director, Global Medical Safety  
Population Council  
[name]  
Washington, DC 20008  
[contact]  
[[contact]](mailto:[contact])

## 14.6 Unblinding Procedures (randomized period only)

Although it is advantageous to retain the blind for all subjects prior to final study analysis, when a serious adverse reaction (serious, unexpected and related to the investigational product) is judged reportable on an expedited basis, the blinding should be broken for the subject. Only interventions determined to be active will be reported to the FDA by the Sponsor. Unblinded interventions of placebo do not need to be reported to the FDA.

A statistician not involved in the trial will generate and be responsible for keeping the randomization schedule. Investigators must submit all unblinding requests for SAEs to the Population Council for evaluation and final decision. The decision to unblind will be made by the Sponsor, in consultation with the site Investigator.

The Medical Safety Director, a physician or their designee will determine immediately within 24 hours or at the earliest possible time if the blind should be broken.

The Medical Safety Director will provide written authorization to Regulatory Affairs, the "Holder" of the randomization schedule or their designee to break the blind and notify in writing the study PI immediately within 24 hours.

If the blind is broken (e.g., for reasons of subject safety only) and determined to be an active intervention, these cases should be reported to the FDA in an IND safety report according to 21 CFR 312.32(c).

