### 9.8.2 Prohibited

- 1) Any hormonal contraceptive other than combined OC pill or patch (OL); NuvaRing® (randomized)
- 2) Barrier contraceptives: condoms (male or female), sponge, diaphragm, cervical cap
- 3) Vaginal and rectal products (including, but not limited to vaginal medications, spermicidal products, lubricants, douches)
- 4) ARV therapy for prevention or treatment
- 5) HSV-2 treatments: Acyclovir, valacyclovir or other medication
- 6) Systemic steroids
- 7) Systemic antibiotics
- 8) Antihypertensive medications, including diuretics
- 9) Investigational therapies for any medical condition
- 10) Mannose (unless used as treatment for a severe reaction; See 15.4)

If a subject is taking any medication that is not included in the lists above, the Investigator should contact the Population Council Study Manager prior to enrollment.

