Both gels will be packaged in identical overwraps with labeling that identifies the protocol number, sponsor, storage conditions, and investigational use warning as required by the FDA. In the OL period, gels will be labeled as PC-6500 investigational gel material. In the randomized period, study gels will be labeled as either PC-6500 or PC-535 placebo without indicating which specific gel is within. The contents will be specified via a randomized code known only to the sponsor/manufacture. The subjects, study coordinator, laboratory staff, and statisticians will not be informed as to the product assignment of the subjects.

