## 15.4 Management of Specific Toxicities

There are no known specific toxicities of GRFT, but because it is a mannose binding lectin, mannose could be an antidote for unexpected toxicity.

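### In an emergency the treating investigator has no assured, timely access to a woman's assignment: the sponsor decides on unblinding and holds the code, and no emergency route is given

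*Protocol*

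**What the plan says.** All references are to the protocol and concern the randomized period.

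- **Who decides (14.6).** "Investigators must submit all unblinding requests for SAEs to the Population Council for evaluation and final decision". The next sentence adds: "The decision to unblind will be made by the Sponsor, in consultation with the site Investigator".
- **How fast (14.6).** The Medical Safety Director or a designee "will determine immediately within 24 hours or at the earliest possible time if the blind should be broken". The director then gives written authorization "to break the blind and notify in writing the study PI immediately within 24 hours".
- **When (14.6).** The section opens with the case in which the blind should be broken: a serious, unexpected, product-related reaction that qualifies for expedited reporting. Its last paragraph also mentions, as an example, a blind broken purely for a subject's safety.
- **Who holds the code.** Section 9.11: "The contents will be specified via a randomized code known only to the sponsor/manufacture". Section 14.6 first gives custody of the schedule to a statistician outside the trial, and later refers to Regulatory Affairs and a holder or designee.
- **Emergencies (14.5).** "the Investigator will use medical judgment and remove the subject from immediate harm". The investigator notifies afterwards and needs no prior sponsor approval for an emergency deviation. Access to the code is not mentioned.
- **Mannose.** Section 15.4 says GRFT has no known specific toxicities but that "because it is a mannose binding lectin, mannose could be an antidote for unexpected toxicity". Section 9.8.2 lists as prohibited: "Mannose (unless used as treatment for a severe reaction; See 15.4". The exception is not tied to treatment arm.

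**The concern.** Unblinding serves two purposes. One is regulatory: deciding whether an event on active product must go to the FDA. A sponsor-controlled process measured in hours suits that. The other is clinical: telling the person treating an ill woman what she received. That needs an answer within the time frame of the emergency.

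Section 14.6 acknowledges the second purpose but routes every investigator request for an SAE through the process built for the first. The investigator is consulted but does not decide, the code is not at the site, and the answer passes through a decision, a written authorization and a written notice.

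This is the first trial of GRFT in humans, and nine of the 14 doses are taken at home. PC-535 is the same formulation without GRFT, so the rationale in 15.4 for mannose as a possible antidote applies only to the active arm. At stake is whether a decision about an individual woman, or the work-up of her event, has to be made without a fact that the sponsor holds.

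**Working it through.** No sample-size or error-rate calculation applies. The check sets the sections side by side and adds up the stated limits.

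**1. Can the investigator treat at once?** Yes. Section 14.5 calls for immediate action on medical judgment, and 9.8.2 permits mannose for a severe reaction without reference to arm. Neither waits for 14.6.

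**2. Can the investigator learn the assignment at once?** Not by any route in the protocol.
- 14.6: the request goes to the sponsor, which has the final say.
- 9.11: the code is with the sponsor or manufacturer.
- 9.5 and 9.7: kits are numbered and dispensed through the site pharmacy, but the randomization numbers do not identify the product and the pharmacy is given no code.
- 14.5: prior approval for deviations is waived in an emergency. That does not help, because permission to deviate does not supply a code the site does not hold. The section names a contact for the Medical Safety Director, but under 14.6 that director must in turn authorize another party to open the code.

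**3. Who opens the code?** Section 14.6 gives two descriptions: an outside statistician who keeps the schedule, and later Regulatory Affairs and a holder or designee. The second can be read as one party or as several. A site with an urgent request could not tell from the text who is able to answer it.

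**4. How long could it take?** The stated limits are 24 h for the decision and 24 h for written notice to the principal investigator. The start of the second clock is not given.
- If both run from the request: at most 24 h.
- If the second starts at the decision: 24 h + 24 h = at most 48 h.

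Both are ceilings. The text also asks for immediate action.

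**5. How uncertain is the assignment meanwhile?** The plan in 9.4 and 9.5 is up to 14 active and up to 6 placebo.
- Planned chance of active gel: 14/20 = 70%.
- Planned chance of placebo: 6/20 = 30%.

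These are planned shares only. Section 9.4 says that all 20 women will not be enrolled and that the remaining assignments are made case by case. Section 9.5 says the final active and placebo tally is unknown until the end of the study.

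**The case against.** The strongest reply is that nothing here conflicts. The investigator treats under 14.5 and sends a request under 14.6 in parallel. That stands. A reader might infer that the two sections cannot both be followed, or that treatment must wait for the sponsor; the text supports neither.

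Three other stronger readings also fail.

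- **That unblinding is allowed only for regulatory reporting.** Expedited reporting is the stated case in which the blind should be broken, but 14.6 itself refers to breaking it for subject safety. What is missing is a route for that case.
- **That a woman on placebo would be harmed by receiving mannose, or that mannose is an established rescue.** Section 15.4 offers it only as a possibility, and no passage describes harm from it. Nor does any passage make a treatment decision depend on arm.
- **That the wait is 48 hours.** That is one reading of two limits, and 24 hours is equally open.

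It can also be said that an emergency procedure may sit in the Study Specific Procedures manual, which is not at hand. That is possible, but neither 14.5 nor 14.6 refers to the manual for unblinding, and a manual procedure that let the site open a code would contradict the sponsor's final decision in 14.6.

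After these concessions one thing remains: the protocol sets a rule for unblinding requests, and that rule gives the treating investigator no dependable access to the assignment in an emergency.

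**Conclusion.** The point holds as a weakness in a stated safety procedure. It is not a contradiction between sections and not a bar to treatment. In an emergency where the assignment bears on care or work-up, the investigator may have to decide without it. Up to 24 hours is allowed for the sponsor's decision alone, and notice may come at up to 24 or 48 hours depending on an unstated clock start. The planned probability that the woman received no GRFT is 30%; the realized share is not known.

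This rests on two assumptions: that no emergency code break is set out in documents not shown, and that knowing the assignment could matter to care or work-up in at least some severe event. The second is a clinical judgment that the protocol neither makes nor excludes. The issue affects no planned estimate or test.

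**What to change.** Reconcile sections 9.8.2, 9.11, 14.5, 14.6 and 15.4 on emergency access to the assignment:

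1. Keep the sponsor's decision for unblinding that serves regulatory reporting, and say when each 24-hour limit starts.
2. Name one holder of the randomization schedule and use that name throughout 14.6 and 9.11.
3. Add a separate emergency route for one subject at a time that the site can reach directly, for example sealed per-kit codes at the site pharmacy for the kits in use. Record each opening with date, time and reason, notify the sponsor afterwards, and keep all other subjects blinded.

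This concerns access to information only. Whether and how any reaction is treated, including any use of mannose, remains for the sponsor and investigator to settle when they reconcile the sections.

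The cost is an amendment to the wording and at most 20 sealed codes, fewer if only the kits still in use are covered. The downside is a slightly higher chance that a single subject is unblinded, which the log makes visible.
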